### Participant timeline {13}

Participant timeline is shown in Table 1.

**Table 1 Tab1:** Schedule of enrolment, interventions, and assessments

Assessment/activity	Online screening/baseline	Telephone interview	Post-randomization		Follow-up		
					***f1***	***f2***	***f3***
	***−t***_***1***_	***t0***	***t***_***1***_***–t***_***8***_ (weekly)	***t***_***9***_ (post)			
Informed consent	X						
Demographic data	X						
ICBT			X				
PHQ-9	X			X	X	X	X
GDS	X			X	X	X	X
GAD-7	X			X	X	X	X
WHO-5	X			X	X	X	X
AUDIT	X			X	X	X	X
M.I.N.I (Depression)		X					
Treatment expectancy		X					
Treatment engagement			X				
NEQ				X			

*M.I.N.I (Depression)* Mini International Neuropsychiatric Interview Depression part, *ICBT* Internet-based cognitive behavior therapy, *GAD-7* Generalized Anxiety Disorder-7, *PHQ-9* Patient Health Questionnaire, *GDS* Geriatric Depression Scale, *WHO-5* World Health Organization Well-Being Index, *AUDIT* Alcohol Use Disorders Identification Test, *F*_*1*_ 3 months, *F*_*2*_ 12 months, *F*_*3*_ 24 months

### Sample size {14}

A power calculation was conducted using GLIMMPLSE software, which is helpful for sample-size calculation for repeated measures and longitudinal studies [33]. Statistical power was set to 0.8, including pre- and post-treatment repeated measurement points; an *α* was set at 0.05. A total sample of 70 participants was needed to reach 80% power. Factoring in an estimated dropout rate of 10% we seek to randomize 78 participants (39 participants in each group). The power analysis is based on the primary outcome variable’s Patient Health Questionnaire (PHQ-9) [29] means and standard deviations of the two time points data based on the results from a similar unpublished study from Sweden (intervention group pre-treatment (T1) *M* = 12.45, *SD* = 4.38, post-treatment (T2) *M* = 6.57, *SD* = 4.34, control group T1 *M* = 14.22, *SD* = 4.19, T2 *M* = 8.11 *SD* = 4.92), with a 1:1 allocation ratio.

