## Objectives {7}

The aim of this study is to test the effectiveness of an Internet-based cognitive behavioral therapy with minimal therapist support for depressed older adults. Our hypothesis is that the treatment group will have significantly larger reductions in symptoms of depression when compared to the waiting list control group post-treatment and will retain these effects at the 3-month follow-up. We will further seek to evaluate retention at 12- and 24-month follow-ups.

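### The planning means show no larger PHQ-9 reduction on treatment (5.88 points) than on control (6.11), so the stated 80% power with 70 participants does not follow from them

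*Protocol article*

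**What the plan says.** Sample size {14} in the protocol article describes a repeated-measures calculation: "Statistical power was set to 0.8, including pre- and post-treatment repeated measurement points", and "an *α* was set at 0.05". The result is that "A total sample of 70 participants was needed to reach 80% power". The allowance for loss follows: "Factoring in an estimated dropout rate of 10% we seek to randomize 78 participants (39 participants in each group").

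The effect comes from PHQ-9 "means and standard deviations of the two time points data based on the results from a similar unpublished study from Sweden". The section prints "intervention group pre-treatment (T1) *M* = 12.45, *SD* = 4.38" for the intervention group, which falls to 6.57 (SD 4.34) after treatment. For the comparator it prints "control group T1 *M* = 14.22, *SD* = 4.19, T2 *M* = 8.11 *SD* = 4.92".

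The effect to be shown is in Objectives {7}: "the treatment group will have significantly larger reductions in symptoms of depression when compared to the waiting list control group post-treatment". Outcomes {12} adds that post-treatment means will be compared between the groups.

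**The concern.** A calculation using both time points, for a hypothesis about larger reductions, should be driven by the difference between the two groups' changes. In the printed data that difference is close to zero and has the wrong sign. The 1.54-point gap after treatment is smaller than the 1.77-point gap already present at baseline, so it does not show a benefit either.

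This paragraph is the only justification given for the trial's size. If its output does not follow from its inputs, a reader cannot tell what effect the trial was sized to detect, and a non-significant result could be misread as coming from an adequately powered trial. The source is unpublished, so readers cannot resolve the conflict themselves. As printed, the planning data also contradict the hypothesis they are meant to support.

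**Working it through.** **Inputs (Sample size {14}).** PHQ-9 mean (SD): intervention 12.45 (4.38) before and 6.57 (4.34) after; control 14.22 (4.19) before and 8.11 (4.92) after. Alpha 0.05, power 0.80, 1:1 allocation, 35 per group before dropout. Sidedness is not stated; two-sided is assumed. The pre-post correlation r is not stated either, so a range is shown. Power is from the noncentral t distribution.

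**What reproduces.** The dropout step does: 70 / 0.9 = 77.8, rounded up to 78. The figure of 70 does not, as follows.

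**1. Difference in change (group by time).**
- Changes: 12.45 - 6.57 = 5.88 on intervention; 14.22 - 8.11 = 6.11 on control. Difference: 5.88 - 6.11 = -0.23.
- Variance of change in each group = SD1² + SD2² - 2·r·SD1·SD2. At r = 0.5 this is 19.01 (intervention) and 21.15 (control), giving a pooled SD of √20.08 = 4.48.
- d = 0.23 / 4.48 = 0.051. Required n per group = 2(1.960 + 0.842)² / d², about 5,960.
- For r = 0.3 to 0.8 the SD of change runs from 5.29 to 2.86 and d from 0.043 to 0.080. Power at 35 per group is 5 to 6%, and about 8,300 down to 2,400 per group would be needed. Even at r = 1 it is about 80 per group.

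**2. Post-treatment means only.**
- Difference 8.11 - 6.57 = 1.54; pooled SD = √((4.34² + 4.92²)/2) = 4.64; d = 0.33.
- Power at 35 per group is 28%; 144 per group are needed. One-sided, power is about 40%, with 113 per group needed.

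**3. Group main effect averaged over both times.**
- Average gap (1.77 + 1.54)/2 = 1.655. SD of a person's two-time average = ½√(SD1² + SD2² + 2·r·SD1·SD2), pooled: 3.16 at r = 0 and 4.23 at r = 0.8.
- d = 0.52 to 0.39, power 58% to 36%, about 58 to 104 per group needed. This contrast counts the baseline imbalance as effect, so it does not test the hypothesis.

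**4. Time effect alone.** The average drop is (5.88 + 6.11)/2 = 5.995 points; fewer than 10 people in total would suffice, and no between-group question is tested.

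| Contrast | Power at 35 per group | Needed per group for 80% |
|---|---|---|
| Difference in change, r = 0.3 to 0.8 | 5 to 6% | about 8,300 to 2,400 |
| Post-treatment means | 28% | 144 |
| Group main effect, r = 0 to 0.8 | 58 to 36% | about 58 to 104 |

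**5. A possible misprint.** If the two baseline means were exchanged, the changes would be 14.22 - 6.57 = 7.65 and 12.45 - 8.11 = 4.34, a difference of 3.31 points. At r of about 0.41 the SD of change is about 4.87, d = 0.68, and 35 per group follows.

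**6. What 35 per group can detect at 80% power.** d = 0.679. Unadjusted: 0.679 × 4.64 = 3.15 PHQ-9 points. Adjusted for baseline at an assumed r = 0.5: 3.15 × √(1 - 0.25) = 2.73 points.

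**The case against.** Four points can be made for the plan.

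- **Some calculation does reach about 35 per group.** Take the 1.54-point post-treatment gap, assume equal baselines as randomisation gives in expectation, and adjust for baseline. The residual SD is 4.64·√(1 - r²); at r = 0.87 it is 2.29 and about 35.6 per group are needed. So it cannot be said that no correlation whatever yields 70. But this route discards two of the four printed means and needs a very high correlation that the article does not state. At r = 0.5 the same route gives 35% power and needs 108 per group.
- **The post-treatment means do favour treatment.** They do, by 1.54 points, and Outcomes {12} plans that comparison. The lack of benefit therefore concerns change from baseline, which is what Objectives {7} hypothesises. On the more favourable reading power is still only 28%.
- **The correlation and the test may be in a fuller document.** That is fair, and their absence is not the complaint. The article prints both inputs and output, and these disagree; for the change contrast no value of r up to 1 repairs it.
- **The trial is labelled exploratory, and recruitment had begun.** Trial design {8} does use that label, but the article also states a directional significance hypothesis and claims 80% power. That recruitment was under way is a reason to leave the target alone, not to leave the claim uncorrected.

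The exchanged-baseline explanation must also be held loosely. It matches at one freely chosen correlation; the same exchange gives about 58 per group at r = 0 and 13 at r = 0.8. It is a reason to check the source, not a diagnosis.

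**Conclusion.** The concern holds. On the printed means and SDs, 70 analysed participants do not give 80% power for a between-group effect under any of contrasts 1 to 3 at correlations of 0 to 0.8. Power is 5 to 6% for the hypothesised contrast, 28% for post-treatment means, and at most 58% for an average over both times that does not address the hypothesis. These figures assume a two-sided 0.05 test and 35 analysed per group; a one-sided test does not rescue the claim.

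Whether the means are misprinted or the calculation tested something else cannot be settled from the article. Either way the paragraph is wrong as it stands and must be corrected, because it states a design property that its own inputs do not deliver. The finding concerns the stated justification; it does not show that 78 is the wrong number to randomise.

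**What to change.** Check the four PHQ-9 means and their group labels against the Swedish data file, then take one of two courses.

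- **If a value or label was misprinted:** correct it, re-run the calculation, and state the pre-post correlation and the hypothesis tested in the power software.
- **If the means are right:** withdraw the statement that 70 participants give 80% power on them and replace it with wording such as: *70 analysed participants give 80% power (two-sided 0.05) for a standardised between-group difference of 0.68, which is about 3.2 PHQ-9 points unadjusted, or about 2.7 points adjusted for baseline if the pre-post correlation is 0.5.* The adjusted figure belongs there only if the analysis will adjust for baseline. This sentence describes what the sample can detect; it does not argue that such a difference is expected or clinically important, so the sponsor should add its reasons for that.

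Keep the target of 78. The cost is one re-run and a change of wording, with no extra participants. The price is a less favourable statement of power or detectable effect.

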### Outcomes {12}

Difference between intervention and control groups pre- and post-treatment as well as at 3-month and 1- and 2-year follow-ups will be analyzed for both primary and secondary outcomes. Primary outcomes are depression symptoms measured with the Patient Health Questionnaire (PHQ-9) [29] and Geriatric Depression Scale (GDS) [30]. Secondary outcomes include anxiety symptoms and psychological well-being. Anxiety symptoms will be measured with the Generalized Anxiety Disorder Scale (GAD-7) [31] and levels of psychological well-being will be measured with the World Health Organization Well-being Index (WHO-5) [32]. Difference in means post-treatment will be compared between groups for both primary and secondary outcomes. Within group trial effects will be calculated using difference in means from baseline to post-treatment for all primary and secondary outcomes. Additionally long-term effectiveness of the intervention will be measured comparing outcome differences from post-treatment to 3-month and 1- and 2-year follow-ups.

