### Methods in analysis to handle protocol non-adherence and any statistical methods to handle missing data {20c}

Initially, intention-to-treat (ITT) analysis will be performed on all primary outcomes in case of drop-out from the study. Secondary per protocol analyses (PPA) will be performed for those participants who adhered to treatment protocol. In ITT analysis last value carried forward will be used to fill in missing data. In PPA analysis missing cases will be removed on a case-by-case basis and only completed data will be analyzed.

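### The step from 70 to 78 preserves 80% power only for observed post-treatment scores, whereas the first-line ITT analysis keeps drop-outs in at their baseline PHQ-9

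*Protocol article*

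**What the plan says.** All references are to the protocol article.

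- Sample size {14}: "Statistical power was set to 0.8, including pre- and post-treatment repeated measurement points", and alpha "was set at 0.05", with no sidedness given. The base figure is: "A total sample of 70 participants was needed to reach 80% power". The allowance for drop-out follows: "Factoring in an estimated dropout rate of 10% we seek to randomize 78 participants (39 participants in each group".
- The missing-data section {20c} puts intention-to-treat first for the primary outcomes and specifies: "In ITT analysis last value carried forward will be used to fill in missing data". Removing missing cases is reserved for the per-protocol analysis, which is secondary.
- Outcomes {12} gives the between-group comparison: "Difference in means post-treatment will be compared between groups for both primary and secondary outcomes".
- Table 1 and section {18a} schedule PHQ-9 at baseline, at post-treatment (t9) and at the three follow-ups. None is scheduled between baseline and t9.

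**The concern.** The sample-size step and the main analysis treat drop-outs in two different ways. Dividing by 0.9 treats them as lost: 78 go in and about 70 are analysed. The carry-forward rule treats them as retained: all 78 are analysed, and about 8 of them (10% of 78 = 7.8) enter the post-treatment comparison with their baseline score.

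Those participants show no treatment effect, so the expected difference shrinks, and the gain from 70 to 78 does not make up for it. The 78 is the recruitment target, and the reader takes it to carry the 80%. If the intention-to-treat result were null, it would be read as somewhat better powered than it was.

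This is separate from whether carrying values forward is a good method. The rule in {20c} could stay as it is; the point is that the inflation in {14} was not worked out for it.

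**Working it through.** **Reproducing the plan's figure.** 70/(1 − 0.10) = 77.8, rounded up to 78, or 39 per arm. The arithmetic is right for a complete-case analysis.

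**Inputs from the protocol.** Alpha 0.05; power 0.80; 70 before drop-out (35 per arm); drop-out 10%; 78 randomised (39 per arm); 1:1 allocation.

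**Assumptions.** Two-sided test. Drop-out of 10% in each arm, since the protocol gives one rate and no split. Drop-out unrelated to outcome. PHQ-9 SDs rounded from {14} to 4.3 at baseline and 4.6 post-treatment. Pre-post correlation 0.3 to 0.7, which the protocol does not give.

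**Step 1: the effect implied by 70.** A two-sample t-test with 35 per arm has 80% power at d = 0.679, which is 0.679 × 4.6 = 3.1 PHQ-9 points. This takes 70 as correct; the effect is not stated in the protocol.

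**Step 2: dilution alone.** With 10% of each arm at zero change, the expected difference is 0.9 × 0.679 = 0.611.
- The extra participants raise the signal-to-noise ratio by √(78/70) = 1.056, but 0.9 × 1.056 = 0.95, a net loss.
- Power at 39 per arm with d = 0.611 is 76.0%.
- For scale, 80% at 0.611 needs 43 per arm (86 in all), in line with 70/0.9² = 86.4.

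**Step 3: dilution plus spread, post-treatment means.** If completers in an arm fall by Δ points on average, the variance of the analysed scores in that arm is 0.9 × 4.6² + 0.1 × 4.3² + 0.09 × Δ² = 20.89 + 0.09Δ².
- Waiting list falls 0, intervention 3.1: variances 20.9 and 21.8, average SD 4.62, d = 0.9 × 3.125/4.62 = 0.609.
- Waiting list falls 2, intervention 5.1: variances 21.3 and 23.3, average SD 4.72, d = 0.9 × 3.125/4.72 = 0.596.

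Simulated power at 39 per arm (10% missing per arm, baseline carried forward) is about 76% in the first case and about 74% in the second, with almost no dependence on the correlation.

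**Step 4: change scores instead.** With a static waiting list the carried-forward zeros reduce the spread in that arm, so most of the loss is recovered: simulated power is 79–80%. With a waiting-list fall of 2 points it is about 76–78%.

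**Step 5: unequal drop-out.** Keep 10% overall and a waiting-list fall of 0–2 points.
- 15% missing in the intervention arm and 5% in control: about 61–71% for post-treatment means and 62–75% for change scores.
- 5% and 15%: about 80–84% for post-treatment means and 84–88% for change scores. Where controls improve, part of this is bias towards the intervention, because control drop-outs are held at their worse baseline level.

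**The case against.** **The step is conventional and reproduces.** This stands. Dividing by one minus the drop-out rate is ordinary practice, and {14} attaches 80% to the 70, not in so many words to 78 under a carried-forward analysis. It is therefore not an arithmetic slip. It is a mismatch with the analysis that {20c} puts first.

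**The loss can almost vanish.** This also stands in part. The power calculation refers to repeated pre and post measurements, which is closer to a change-score or group-by-time test, and with a static waiting list that loses less than one point. But {12} names post-treatment means as the between-group comparison, and there the loss is about four points or more under equal drop-out.

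**A reader might infer a fall to 67%.** Setting the waiting-list improvement at the 6.11 points in the planning data (14.22 − 8.11) does give about 67% for post-treatment means. That combines incompatible premises. An effect of 0.68 on top of a 6.11-point control fall requires the intervention arm to fall about 9.2 points, whereas the planning data give 5.88 (12.45 − 6.57). The same data give a post-treatment difference of only 8.11 − 6.57 = 1.54, or 1.54/4.64 = 0.33 SD. They cannot be set aside to obtain 0.68 and then cited for the control fall. What survives is the direction: the more both arms improve, the larger the loss.

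**A reader might also infer that 78 always falls short.** The documents do not support that either. They give no split of drop-out by arm, and with more drop-out among controls nominal power can exceed 80%.

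**The base figure is itself in doubt.** True, and a separate matter. With the stated post-treatment means and SDs, 39 per arm gives about 30% power with full data and about 26% after dilution. Correcting 70 would not cure this point, because a new base figure divided by 0.9 would meet the same mismatch.

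**Conclusion.** The inconsistency is in the text: {14} inflates for an analysis of observed post-treatment scores, while {20c} leads with an analysis that keeps everyone, drop-outs at baseline. The size is moderate. Conditional on 70 being right, a two-sided 0.05 test and 10% drop-out in each arm, the power of 78 for the comparison of post-treatment means drops from 80% to about 76% by dilution, or 74–76% with the spread included and a waiting-list improvement of 0–2 points. It would be lower if both arms improve more, nearly 80% for change scores with a static waiting list, and either side of 80% if drop-out is unequal. The direction under equal drop-out is firm. No single power figure is, because the effect of 0.68 is back-calculated from 70 and is not supported by the stated means and SDs.

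**What to change.** In Sample size {14}, do one of the following.

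1. State that 80% power with 78 randomised refers to an analysis of observed post-treatment (t9) PHQ-9 scores, and name that analysis as the one the sample size serves.
2. Recompute the power of 78 for the carried-forward intention-to-treat comparison from the planning inputs actually used, and report it with the assumed drop-out in each arm, the test and its sidedness.

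Do not insert a fixed range such as 67–76%: it rests on an effect of 0.68 that the published planning values do not yield, and on those values it would overstate power more than twofold (about 26–30%).

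The cost is one or two sentences and, under the second option, one recalculation. No extra enrolment is needed. The drawback is that the stated power is likely to be less favourable, or tied to an analysis other than the one {20c} puts first.

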### Recruitment {15}

Participants will be recruited through social media outlets, a press release and advertisement in local papers, interviews on radio, and local television. In order to obtain a needed sample size, recruitment period might be prolonged and paid advertisement in social media targeting older adults might be intensified.

## Assignment of interventions: allocation

### Sequence generation {16a}

An independent researcher will use a random number generator (random.org) to randomly assign all participants at a 1:1 ratio to study groups without stratification.

### Concealment mechanism {16b}

No concealment will be used because it is not possible due to the nature of the trial design.

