### Eligibility criteria {10}

Inclusion criteria: Participants eligible for the trial must comply with all of the following at randomization: (1) 60+ years, (2) depressive symptoms, (3) access to a computer/tablet/smartphone and to the Internet, and (4) good knowledge of the Lithuanian language (reading, speaking, and writing without an interpreter). Exclusion criteria: (1) problematic alcohol use, (2) presently in any other psychological treatment, (3) severe depression, (4) suicidal ideation, and (5) significant change in psychiatric medication (during last 6 weeks).

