### Implementation {16c}

All participants will be self-referred. Participants will be enrolled and assigned to trial groups by different study team members (Fig. 1).

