## Assignment of interventions: blinding

### Who will be blinded {17a}

Due to the nature of the psychological intervention no one from the participants and study team members will be blinded after assignment to intervention. Only data analysts will be blinded to the study groups until all data analyses are completed.

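### The protocol rules out allocation concealment on a ground that does not hold, so as written the randomisation must be read as unconcealed

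*Protocol article*

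**What the plan says.** All of this is in the protocol article.

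- **Concealment mechanism {16b}** consists of one sentence: "No concealment will be used because it is not possible due to the nature of the trial design".
- **Sequence generation {16a}** describes the procedure as follows: "An independent researcher will use a random number generator (random.org) to randomly assign all participants at a 1:1 ratio". There is no stratification, and no blocking is mentioned.
- **Implementation {16c}** separates the roles: "Participants will be enrolled and assigned to trial groups by different study team members". It refers to a flow diagram that is not reproduced in the text available here.
- **Who will be blinded {17a}** gives a similar reason for the open treatment: "Due to the nature of the psychological intervention no one from the participants and study team members will be blinded after assignment to intervention". It then makes one exception, for the analysis: "Only data analysts will be blinded to the study groups until all data analyses are completed".
- **Eligibility criteria {10}** must be met at randomisation. The exclusions include severe depression, suicidal ideation and problematic alcohol use.
- **Table 1** (Participant timeline {13}) places a telephone interview, with the depression part of the M.I.N.I. and treatment expectancy, before the post-randomisation columns.

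**The concern.** Concealment and blinding protect different periods. Concealment keeps whoever decides on entry from knowing the next allocation until that decision is final. Blinding concerns what people know afterwards. The first can be achieved in any trial where someone other than the enrolling staff can hold the list, whether or not treatment is open. A waiting-list comparator does not alter that.

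This is more than a missing detail. The section reserved for the topic states that concealment will not be used and calls it impossible. A trial run to that rule could let staff know the coming allocation while they are still interviewing a candidate and deciding on eligibility.

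The stakes are higher here because other protections are few. Participants and the study team are unblinded, and all questionnaires are self-reported. The blinding of analysts comes too late to protect enrolment. Concealment is therefore the main remaining safeguard for the comparability of the groups at entry. Treatment expectancy is recorded at the same interview and is the predictor in a planned regression, so foreknowledge could affect that measure as well.

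**Working it through.** The point depends on no stated figure, so there is no figure to reproduce. The check is to read the sections against each other.

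**1. Is the stated reason valid?** {16b} rests on the nature of the design. The relevant features are an open intervention and a waiting list. Both make the allocation evident once it is given, and {17a} says as much: "no one from the participants and study team members will be blinded after assignment to intervention". Neither makes it evident beforehand. The reason therefore supports the absence of blinding but not the absence of concealment.

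**2. Do other sections supply concealment anyway?** {16a} gives randomisation to an independent researcher, and {16c} separates enrolment from assignment. These are the usual components of a concealed procedure. Two things are missing: a statement that enrolling staff cannot see the sequence, and a statement that an allocation is released only after eligibility is recorded. {16a} and {16c} also leave unclear who assigns, the independent researcher or a member of the study team. Given an express disclaimer in {16b}, concealment cannot be inferred from the separation of roles.

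**3. Is there a route for bias?** Staff speak to each candidate before randomisation (Table 1) and apply exclusions for which no decision rule is stated, such as severe depression and suicidal ideation ({10}). If the next allocation were visible, it could influence who is admitted.

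**4. Size.** The document gives nothing from which to estimate the bias. The following is an illustration under assumptions only.

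- Assumed: no true effect, 35 analysed per arm (half of the 70 in Sample size {14}), a two-sided 5% test of post-treatment PHQ-9 means, and a bias b in the difference.
- Pooled post-treatment SD from {14}: √[(4.34² + 4.92²)/2] = 4.64.
- Standard error: 4.64 × √(2/35) = 1.11.
- Rejection rate: Φ(b/1.11 − 1.96) + Φ(−b/1.11 − 1.96).

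| Assumed b (PHQ-9 points) | Rejection rate |
|---|---|
| 0.5 | about 7% |
| 1.0 | about 15% |
| 1.5 | about 27% |
| 2.0 | about 44% |

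Nothing in the document says which row, if any, applies.

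**5. Effect of the fix on the design.** None. 70/0.9 = 77.8, rounded up to 78, agrees with {14} and stays as it is, as do alpha, power and the 1:1 ratio.

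**The case against.** The strongest reply is that the sentence may be badly worded while the procedure is sound. An independent researcher randomises, and enrolment and assignment are separate. With no blocks or strata mentioned, the next allocation is hard to guess unless the list is visible. Baseline questionnaires are completed online before randomisation, and {17a} denies blinding only after assignment. The document does not exclude randomisation in one batch after enrolment, which would be concealed. This stands as a limit on the claim. It does not rescue {16b}, which says the opposite and gives an invalid reason.

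Several stronger readings are tempting, and the document does not support them:

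- **That enrolling staff did know the allocations, or that selection bias occurred.** No section says so. What is established is a wrong rule and the exposure it would create.
- **That the authors confused concealment with blinding.** The similar reasoning in {16b} and {17a} suggests it, but one refers to the trial design and the other to the psychological intervention. It remains an inference, and the stated reason is wrong either way.
- **That every exclusion is a matter of judgement.** AUDIT is scheduled at online screening, so problematic alcohol use may be decided by a score.
- **That a plausible bias can be sized against the planning difference of 8.11 − 6.57 = 1.54 points.** That difference is not a clean treatment effect. The planning data in {14} carry a baseline difference of 14.22 − 12.45 = 1.77 in the same direction. Mean improvement is 12.45 − 6.57 = 5.88 with intervention and 14.22 − 8.11 = 6.11 with control, which favours control by 0.23.

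**Conclusion.** The sentence in {16b} is wrong and needs correcting. Concealment is possible in this design, and no other section states that it is in place, so a reader must treat the randomisation as unconcealed. The exposed stage is the telephone interview and the eligibility decision. The separation of roles lowers the risk and may amount to concealment in practice, but the document does not establish that.

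The size of any bias is unknown. The illustrative rejection rates rest entirely on an assumed bias and show only that a shift of one or two points would matter in a trial of this size. A measured baseline imbalance could be seen and adjusted for. Selection on unmeasured prognosis could not.

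**What to change.** Replace the sentence in {16b} with a rule to this effect: *The independent researcher alone holds the allocation sequence and releases each allocation only after consent, baseline questionnaires, telephone interview and the eligibility decision have been recorded on the platform. Staff who enrol have no access to the sequence.* Bring {16a} and {16c} into line on who assigns.

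Timing matters. Trial status says that recruitment began on 28 January 2021 and was planned to run to May 2021, and the article appeared on 16 December 2021. For participants already randomised, the rule may be given as a description only if it is what happened. For them, state:

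- who held the sequence;
- when allocations were released relative to the recorded eligibility decision;
- whether enrolling staff had access;
- whether randomisation was done in a batch after enrolment, which counts as concealed.

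If allocations were visible to enrolling staff, report this as a limitation in the Discussion, which at present names the waiting-list control and self-referral but not this.

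The cost is negligible: a few sentences, using an independent researcher and a platform that already exist.
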